## Serious Adverse Events

An SAE is any untoward medical occurrence that at any dose:

- Results in death.
- Is life-threatening.

(Note: The term “life-threatening” refers to an event in which the subject is at risk of death at the time of the event, not an event that hypothetically might have caused death if it was more severe.)

- Requires inpatient hospitalization or prolongs an existing hospitalization.
- Results in persistent or significant disability or incapacity.
- Is a congenital anomaly or birth defect.
- Is otherwise considered as medically important.

(Note: Important medical events that may not result in death, be life-threatening, or require hospitalization may be considered as SAEs when, based upon appropriate medical judgment, they may jeopardize the subject or may require medical or surgical intervention to prevent one of the outcomes listed above. Examples of such events include allergic bronchospasm requiring intensive treatment in an emergency room or at home, blood dyscrasias or convulsions that do not result in inpatient hospitalization)

For the purposes of reporting, any suspected transmission of an infectious agent via an IMP is also considered an SAE, as described in 7.4.1.4

## Events that Do Not Meet the Definition of an SAE

Elective hospitalizations to administer, or to simplify trial treatment or trial procedures (for example, an overnight stay to facilitate chemotherapy and related hydration therapy application) are not considered SAEs. However, all events leading to unplanned hospitalizations or unplanned prolongation of an elective hospitalization (for example, undesirable effects of any administered treatment) must be documented and reported as SAEs.

## Events Not to Be Considered as AEs/SAEs

Medical conditions present at the initial trial visit that do not worsen in severity or frequency during the trial are defined as Baseline Medical Conditions, and are not to be considered AEs.

### 7.4.1.2            Methods of Recording and Assessing Adverse Events

On both visit days, the subject and the parents / representatives will be queried on changes in his or her condition by questioning. During the reporting period, any unfavorable changes in the subject's condition will be recorded as AEs, whether reported by the subject or observed by the investigator.

Complete, accurate and consistent data on all AEs experienced for the duration of the reporting period (defined below) will be reported on an ongoing basis in the appropriate section of the CRF. All SAEs must be additionally documented and reported using the appropriate Serious Adverse Event Report Form as described in Section 7.4.1.4

It is important that each AE report include a description of the event, its duration (onset and resolution dates and times, its severity, its causal relationship with the trial treatment, any other potential causal factors, any treatment given or other action taken, and its outcome. In addition, serious cases should be identified and the appropriate seriousness criteria documented.

Specific guidance can be found in the CRF Completion and Monitoring Conventions provided by the project management.

An AE monitoring and reporting system for this study will be implemented according to study specific instructions developed based on this protocol.

### **7.4.1.3 Definition of the Adverse Event Reporting Period**

The AE reporting period for safety surveillance begins when the subject is initially included in the trial (date of signature of informed consent) and continues until the visit of Day 2.

Any SAE assessed as related to the used IMPs must be reported whenever it occurs, irrespective of the time elapsed since the last administration of the IMP.

### **7.4.1.4 Procedure for Reporting Serious Adverse Events**

#### **Serious Adverse Events**

In the event of any new SAE occurring during the reporting period, the Investigator must immediately (within a maximum of 24 HOURS after becoming aware of the event) inform the Sponsor or its designee and the Safety Monitoring Committee in writing.

All written reports should be transmitted using the SAE Report Form, which must be completed by the Investigator following specific completion instructions.

In exceptional circumstances, an SAE (or follow-up information) may be reported by telephone; In these cases, a written report must be sent immediately thereafter by fax or e-mail. Names, addresses, and telephone and fax numbers for SAE reporting will be included in the trial-specific SAE Report Form and other instructions.

Relevant pages from the CRF may be provided in parallel (for example, medical history, concomitant drugs). Additional documents may be provided by the Investigator, if available (for example, laboratory results, hospital report and autopsy report). In all cases, the information provided on the SAE Report Form must be consistent with the data about the event recorded in the CRF.

The Investigator must respond to any request for follow-up information (for example, additional information, outcome, final evaluation, other records where needed) or to any question the Sponsor/designee may have on the AE within the same timelines as those noted above for initial reports. This is necessary to ensure prompt assessment of the event by the Sponsor or designee and (as applicable) to allow the Sponsor to meet strict regulatory timelines associated with expedited safety reporting obligations. Requests for follow-up will usually be made via the responsible Monitor, although in exceptional circumstances the Global Drug Safety department may contact the Investigator directly to obtain further information or to discuss the event.

#### **7.4.1.5 Safety Reporting to Health Authorities, Independent Ethics Committees/ Institutional Review Boards and Investigators**

The Investigator will send appropriate safety notifications to Health Authorities in accordance with applicable laws and regulations.

The Investigator must comply with any applicable site-specific requirements related to the reporting of SAEs (particularly deaths) involving trial subjects to the IEC/IRB that approved the trial.

In accordance with ICH GCP, the Sponsor/designee will inform the Investigator of “findings that could adversely affect the safety of subjects, impact the conduct of the trial or alter the IEC’s/IRB’s approval/favorable opinion to continue the trial.” In particular and in line with respective regulations, the Sponsor/designee will inform the Investigator of AEs that are both serious and unexpected and are considered to be related to the administered product (“suspected unexpected serious adverse reactions” or SUSARs). The Investigator should place copies of Safety Reports in the Investigator Site File. National regulations with regard to Safety Report notifications to Investigators will be taken into account.

All SAEs that are related to study participation (e.g. procedures, a change from existing therapy) or are related to a concurrent medication will be recorded from ICF signature until discharge

All SAE reports and/or all SAE participants-related safety information should be sent to Merck Serono Global Drug Safety Department:

[contact]

[contact]

[contact]

The SAE will be summarized and reported to IRBs by the PI in the required time frame as specified by the IRB. The PI and/or the Sponsor will report the SAE to TFDA.

A written report of the SAE by the study site will be submitted within 24 hours for fatal and life threatening SAEs by phone, followed by paper reports within 7 calendar days of the investigator becoming aware of the SAE on the sponsor SAE report form, containing the minimal required information. All other cases should be reported within 14 days in order to comply with regulations mandating sponsor notification of specified SAEs to TFDA within 7 calendar days

When specifically required by regulations and guidelines, the Sponsor/designee will provide appropriate Safety Reports directly to the concerned lead IEC/IRB and will maintain records of these notifications. When direct reporting is not clearly defined by national or site-specific regulations, the Investigator will be responsible for promptly notifying the concerned IEC/IRB of any Safety Reports provided by the Sponsor/designee and of filing copies of all related correspondence in the Investigator Site File.

#### **7.4.1.6 Monitoring of Subjects with Adverse Events**

AEs are recorded and assessed continuously throughout the trial (see Section 7.4.1.3) and are assessed for final outcome at the Day 2. All SAEs ongoing must be monitored and followed up by the Investigator until stabilization or until the outcome is known, unless the subject is documented as “lost to follow-up”. Reasonable attempts to obtain this information must be made and documented. It is also the responsibility of the Investigator to ensure that any necessary additional therapeutic measures and follow-up procedures are performed.

#### **7.4.2 Vital Signs, Physical Examinations, and Other Assessments**

During screening and on Day 1 and Day 2 before the first and after the last taste assessment a physical examination and the vital signs as respiratory rate, heart rate and temperature are evaluated to make sure that the volunteer is able to do the taste assessment or at the end of the day can be discharged to go home.

Any abnormalities will be reported in the corresponding section in the CRF.

### **8 Statistics**

A Statistical Analysis Plan (SAP) will provide full details of the analyses, data displays, and algorithms to be used for data derivations.

#### **8.1 Sample Size**

A total sample size of 48 subjects is considered adequate to fulfil the objective of the study.

Considering the design Day 1 (2 treatments), Day 2 (3 treatments) with the fact that the same subjects will be treated in both days, the stratification constraint by sex (female/male 1:1 ratio) and age (<9 yrs and ≥9yrs 1:1 ratio), the sample size should be a multiple of 24.

DAY 1: A total of 48 subjects (24 subjects per sequence) will provide at least 89.2% power to detect a 10 pts mean difference in VAS overall palatability between Rac-PZQ ODT (no water) and L-PZQ ODT (no water), assuming a within-subject standard deviation of 15 pts (square root of within subject MSE), and a two-sided type 1 error of 5.0%.

DAY 2: A total of 48 subjects (8 subjects per sequence, 6 sequences due to 3 treatments-3 periods) will provided at least 92.4% power to detect a 20 pts mean difference in VAS overall palatability between one of the new formulations Rac-PZQ (with water) or L-PZQ (with water) and the current PZQ formulation crushed in water, assuming a within-subject standard deviation

of 15 pts (square root of within subject MSE), and a two-sided type 1 error of 2.5%, to adjust for the multiplicity.

Software East 6.2 was used for the sample size calculation.

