A 1;1 ratio of gender based random assignment will ensure equal distribution of subjects' in groups of equal age categories. Each individual will taste each preparation once making up 5 periods for each sequence of the palatability assessment during the two study days (see Table below)

According to the gender and age each subject will be randomized to one of the sequences.

| DAY 1    |          |          |
|----------|----------|----------|
| PERIOD 1 |          | PERIOD 2 |
| A        |          | B        |
| B        |          | A        |
| DAY 2    |          |          |
| PERIOD 3 | PERIOD 4 | PERIOD 5 |
| C        | D        | E        |
| C        | E        | D        |
| D        | E        | C        |
| D        | C        | E        |
| E        | C        | D        |
| E        | D        | C        |

- A) L-PZQ ODT put and disintegrated in the mouth without water
- B) Rac-PZQ ODT put and disintegrated in the mouth without water.
- C) L-PZQ ODT dispersed in water.
- D) Rac-PZQ ODT dispersed in water
- E) Current PZQ formulation 150 mg crushed in water

For every taste, immediately after spitting and 2-5 min thereafter, the child will be asked to put a mark along the line of the 100 mm visual analogue scale (VAS) incorporating a 5 points hedonic scale. An open ended questionnaire (description of mouth feeling and taste description) will be conducted. A detailed description of the assessment is available in section 7/Appendix III.

After the trial a therapeutic dose of Praziquantel will be made available to the local health council and management team to provide to the participating school.

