### **8.5.2 Analysis of Primary Endpoints**

VAS at time t0 will be summarized using descriptive statistics (mean, median, standard deviation, quartiles (25th, 75th), minimum, maximum) by treatment group.

The first alternative hypothesis (HA1) that the two formulations Rac-PZQ (no water) and L-PZQ (no water) differ in taste, as opposed to the H01 (the two formulations are similar) will be tested using a repeated measure ANOVA with factors time, sequence, treatment and stratification factor of sex and age (in categories). A contrast statement at Time 0 to compare the two formulation based on the likelihood ratio test will be conducted at two-sided 5% significance level.

The second alternative hypothesis (HA2) that at least one of the two new formulations (with water) differs in taste from the “current PZQ formulation” will be tested using a repeated measure ANOVA with factors time, sequence and treatment and stratification factor of sex and age (in categories) will be used.

Contrast statement at Time 0 to compare

- Rac-PZQ ODT (with water) vs current PZQ (crushed with water), and
- L-PZQ ODT (with water) vs current PZQ (crushed with water)

It will be done using the likelihood ratio test. These tests will be performed at an alpha level of 2.5% to account for the multiplicity of testing.

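### The Day 2 power of 92.4% for a 20-point difference does not follow from its stated inputs, which give more than 99.99% in the planned crossover

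*Protocol*

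**What the plan says.** Protocol section 8.1 (Sample Size) gives one power statement for each day.

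- **Day 1** (two products, no water): "A total of 48 subjects (24 subjects per sequence) will provide at least 89.2% power to detect a 10 pts mean difference". The inputs behind this are a within-subject SD of 15 and a two-sided alpha of 5%.
- **Day 2** (three products in water): the same 48 children are spread over six sequences of eight. The claim is that this number "will provided at least 92.4% power to detect a 20 pts mean difference in VAS overall palatability between one of the new formulations" and the current tablet. The inputs given are a within-subject SD "of 15 pts (square root of within subject MSE), and a two-sided type 1 error of 2.5%, to adjust for the multiplicity".

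Section 5.1 confirms that both days are within-child comparisons: "Each individual will taste each preparation once making up 5 periods for each sequence of the palatability assessment during the two study days". Section 8.5.2 uses the same Day 2 significance level for the two contrasts against the current tablet: "These tests will be performed at an alpha level of 2.5% to account for the multiplicity of testing". Section 8.1 names East 6.2 as the software but gives no module or settings.

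**The concern.** The two statements share the same 48 children, the same within-subject SD of 15 (defined both times as the root of the within-subject mean square error) and the same crossover principle. Day 2 differs in two ways: the assumed difference doubles from 10 to 20 points, and alpha falls from 5% to 2.5%. Doubling the difference at an unchanged standard error outweighs that change in alpha many times over, so power should rise from 89.2% to almost 100%. The stated rise is only to 92.4%.

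The Day 2 sentence is the planning basis for the second primary hypothesis (HA2). Either the output is wrong, or one of its inputs (difference, SD or design) is not the one used. The first case understates what Day 2 can detect. In the second, if the SD actually used was larger, the Day 1 power is in doubt as well.

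**Working it through.** **Inputs, all from Protocol section 8.1 unless noted**

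- n = 48 children on each day; each child tastes each product once (section 5.1)
- Within-subject SD = 15 on both days
- Day 1: difference 10, two-sided alpha 0.05
- Day 2: difference 20, two-sided alpha 0.025 per contrast (also section 8.5.2)
- No allowance for dropout, because non-completers are replaced (section 5.4)

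**Formula.** In a crossover where each child provides one value per product, the standard error of a difference between two products is SE = SD × √(2/n). Power is the probability that a noncentral t variable with noncentrality (difference / SE) exceeds the two-sided critical value.

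SE = 15 × √(2/48) = 3.06 on both days.

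**Step 1: reproduce Day 1.** Noncentrality = 10 / 3.06 = 3.27. With 48 − 2 = 46 df and alpha 0.05, power is **89.2%**, exactly as stated. This establishes how the protocol uses its SD.

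**Step 2: apply the same formula to Day 2.** Noncentrality = 20 / 3.06 = 6.53. There are 144 observations. After removing 1 for the mean, 47 for children, 2 for periods and 2 for products, 92 df remain. At alpha 0.025, power is **99.999%** (99.998% with only 46 df). The stated figure is 92.4%.

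**Step 3: look for a crossover reading that gives 92.4% at 20 points with 48 children.**

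| Variant | Power |
|---|---|
| Alpha 0.05 or 0.0125 | above 99.99% |
| Carry-over adjustment (variance × 1.25) | 99.98% |
| Omnibus F test | above 99.99% |
| SD inflated to 15 × √2 | 99.0% |

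None comes near the stated figure.

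**Step 4: what would have to change to give 92.4%.** Changing one input at a time in the crossover:

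- a within-subject SD of about 26.3 instead of 15; or
- a difference of about 11.4 points instead of 20; or
- about 16 to 17 children instead of 48.

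With SD 26.3 on Day 1, the SE is 26.3 × √(2/48) = 5.37 and power for 10 points is about 45%, not 89.2%.

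**Step 5: a possible origin.** If the 48 are split into three independent groups of 48/3 = 16, the SE is 15 × √(2/16) = 5.30 and the noncentrality is 20 / 5.30 = 3.77. At alpha 0.025 this gives 91.5% (two-sample t, 30 df), 92.3% (contrast in a three-group ANOVA, 45 df) or 93.7% (normal approximation).

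**Step 6: what Day 2 can detect on the stated inputs** (SE 3.06, 92 df, alpha 0.025)

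| Difference | Power |
|---|---|
| 10 points | 83.6% |
| 10.9 points | 90% |
| 11.4 points | 92.4% |
| 20 points | 99.999% |

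**The case against.** The strongest case for leaving the sentence alone has four parts.

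1. **The figure is given as a lower bound, so it is literally true.** Day 1 uses the same phrase, "will provide at least 89.2% power to detect a 10 pts mean difference in VAS overall palatability", and there it is the exact crossover power to one decimal. A reader will take a Day 2 figure quoted to 0.1% in the same way. This objection does not stand.

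2. **The error is conservative and changes nothing in the trial.** If the stated inputs are right, this stands. Power for 20 points is higher than claimed, Day 1 supports 48 on its own, and section 8.1 also requires a multiple of 24. No test, contrast or significance level in section 8.5.2 depends on the 92.4%. The reassurance fails only if the figure came from a larger SD.

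3. **The 20 points may be a deliberate planning value.** The protocol does not call 20 points a minimum detectable or required difference, and a larger gap against the current tablet than between two sweetened ODTs is plausible. That stands as far as it goes. But the power attached to 20 points is still wrong, and beside the Day 1 statement it suggests that Day 2 is far less sensitive than it is.

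4. **The three-groups-of-16 explanation is conjecture.** This stands. None of the versions tried returns 92.4% exactly, and a crossover with SD 15 × √3 = 26.0 has the same standard error and fits about as well (92.3% at 46 df, 93.0% at 92 df). The protocol does not show which input or setting was at fault. The discrepancy does not depend on its origin.

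**Conclusion.** The concern holds. On the protocol's own inputs, Day 2 power for 20 points is 99.999%, against a stated 92.4%. The implied type II error is about 0.001% where the text gives 7.6%. This rests on the stated design (each of 48 children tastes all three products), the stated within-subject SD of 15 and two-sided alpha of 2.5%. It does not depend on the choice of degrees of freedom or on allowing for carry-over.

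If those inputs are right, the sample size of 48 is adequate and the sentence understates Day 2: 90% power is reached at about 10.9 points, close to the Day 1 planning difference. A non-significant Day 2 contrast would then say more against differences between about 11 and 20 points than the stated power suggests. If the inputs are not the ones used, and in particular if the SD was nearer 26, the Day 1 claim of 89.2% falls to about 45%. The protocol alone does not show which case applies, so the number must be traced and corrected.

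**What to change.** Retrieve the East 6.2 run for Day 2 and check its design setting, SD, difference and alpha against section 8.1. Then take one of two routes.

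- **If the stated inputs are the intended ones,** restate the Day 2 power for the within-child comparison. If 20 points is kept as the planning difference, give power as above 99.9%. It would be more informative to add what the design can detect, for example: *48 subjects give 90% power for an 11-point difference, and 84% for 10 points, at two-sided 2.5% with a within-subject SD of 15.*
- **If a different SD, difference or design was used for Day 2,** state it and give the reason. If the SD was larger, recalculate the Day 1 power with it, or explain why the two days should differ.

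Naming the East module and settings in section 8.1 would let a reader reproduce both figures. The cost is one corrected sentence and one software run. If the stated inputs are confirmed, the sample size, randomization, conduct and analysis stay as they are.

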## 8.2 Randomization

Subjects will be randomized in blocks by sex (male/female 1:1 ratio) and age (<9 yrs and ≥9yrs 1:1 ratio) in one of the following treatment-sequence

Day 1: 2 treatments (no water) - 2 period cross-over

F1: Rac-PZQ ODT - L-PZQ ODT

G1: L-PZQ ODT - Rac-PZQ ODT

Day 2: 3 treatments (dispersed/crushed in water) - 3 period cross-over

H2: L-PZQ ODT - Rac-PZQ ODT- PZQ 150 mg

J2: L-PZQ ODT– PZQ 150 mg - Rac-PZQ ODT

K2: Rac-PZQ ODT– PZQ 150 mg - L-PZQ ODT

L2: Rac-PZQ ODT - L-PZQ ODT – PZQ 150 mg

M2: PZQ 150 mg - L-PZQ ODT- Rac-PZQ ODT

N2: PZQ 150 mg - Rac-PZQ ODT- L-PZQ ODT

The randomization list will be prepared by Swiss TPH.

## 8.3 Endpoints

### 8.3.1 Primary Endpoints

Overall palatability is assessed by putting a mark along the 100 mm visual analogue scale (VAS) that incorporates a 5-point hedonic scale and answering the questionnaire (see Annex III), and High score indicates good tasting.

The primary endpoint is the overall palatability VAS value taken at Time 0 (right after the spit-out of the IMP).

### 8.3.2 Secondary Endpoints

- Overall palatability VAS value at time 2-5min
- Description of mouth feeling and taste description using an open ended questionnaire

- Document discomfort and other observation in relation to acceptance of the study medication.

## **8.4 Analysis Sets**

### **8.4.1 Full Analysis Set**

The Full Analysis Set (FAS) includes all enrolled subjects assigned to study IMP, whether or not they received it.

### **8.4.2 Safety Set**

The Safety Set (SAF) includes all enrolled subjects who received at least one dose of any study drug.

### **8.4.3 Completers Analysis Set**

The Completers Analysis Set (CAS) includes all enrolled subjects who received at least one dose of any study drug and completed the entire study (Day 1 and Day 2).

